#### Phase II: Exploratory trial

**General procedures** The effect of the interRAI PC on the quality of palliative care is evaluated, using a pretest-posttest design with quasi-random assignment to the intervention or control nursing homes. Control nursing homes provide care as usual.

**Setting and participants** Calls for participation are sent out by four umbrella organizations of Flemish nursing homes. An announcement is also made during a national conference for nursing home staff.

Fifteen volunteering nursing homes participate in the study. In the course of one year, these participating nursing homes will fill out the interRAI PC every three months for all residents aged 65 years or older with palliative care needs. The need for palliative care is evaluated by means of the surprise question (‘Would you be surprised if this person was to die within 6 to 12 months?’)
[25, 26]. Based on a list of Flemish nursing homes from the National Institute for Health and Disability Insurance (NIHDI), fifteen care homes which match the intervention nursing homes regarding to facility size, ownership and geographic region are contacted for participation in a control group.

**Intervention** The fifteen experimental nursing homes receive the intervention that is being tested. The intervention consists of 11 steps. The complete intervention is described in Table 
1. The fifteen control nursing homes provide care as usual and therefore do not receive the intervention.

**Sample size** Each year, on average 18 percent of the residents in a nursing home in Flanders, Belgium die
[27]. Based on these data, this study aims at including at least 44 nursing home residents with palliative care needs, in order to detect an effect of the use of the interRAI PC instrument on the identified factors. Calculations are based on a medium effect size of 0.50, a two-sided significance level of 0.05 and a power of 0.90 (using G*Power 3.1.5 software)
[28].

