### Outcome measures

#### The effect of the interRAI PC instrument on the quality of palliative care

The multinational consortium interRAI has developed the interRAI PC instrument in order to improve palliative care for elderly
[17]. In order to test this in practice, the effect of the interRAI PC on the quality of palliative care is evaluated.

**Psychometrics** An effect or impact evaluation assesses changes that can be attributed to a particular intervention, such as a project, program or policy, both the intended ones, as well as ideally the unintended ones
[29].

**Data collection** Before the intervention period starts, both experimental and control nursing homes fill out the Palliative care Outcome Scale (POS) for all nursing home residents with palliative care needs. The POS is a ten-item outcome measure that assesses the quality of care in palliative patients
[30]. The instrument contains items on physical, psychosocial and spiritual aspects. There are two versions of the instrument: the POS-Staff version and the POS-Patient version. In this study, we will use the POS-Staff version. The POS can also be used to assess persons with moderate to severe dementia
[31]. The POS is a multidimensional scale that shows good psychometric properties. By means of the POS, the quality of care can be evaluated
[32].

In addition, the experimental and control nursing homes fill out a Retrospective Information (RI) document. This document will provide data on the number of deaths in the past year, the place of death and the availability of a specific palliative care record.

After one year, both experimental and control nursing homes fill out the Palliative care Outcome Scale (POS) and the Retrospective information (RI) document for all nursing home residents with palliative care needs.

**Analysis** Quantitative data are analyzed with SPSS, using independent analysis of covariance (ANCOVA). Research has shown that ANCOVA with pretest-posttest data is the most appropriate statistical procedure in quasi-randomized control-group designs
[33].

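### The minimum of 44 residents does not give 90% power for the planned two-group ANCOVA at an effect size of 0.50

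*Protocol article*

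**What the plan says.** The sample-size paragraph (Phase II: Exploratory trial) states that "this study aims at including at least 44 nursing home residents with palliative care needs". The inputs follow: "Calculations are based on a medium effect size of 0.50, a two-sided significance level of 0.05 and a power of 0.90", computed "using G*Power 3.1.5 software". The paragraph names no test. It does not say whether 44 is a total or a number per group, and it gives no correlation between pretest and posttest.

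The comparison is between two groups of homes: "The fifteen control nursing homes provide care as usual and therefore do not receive the intervention". Both groups complete the Palliative care Outcome Scale (POS) before the intervention period and again after one year. The analysis paragraph for the effect question reads "Quantitative data are analyzed with SPSS, using independent analysis of covariance (ANCOVA", and it justifies ANCOVA as suited to pretest-posttest data with a control group.

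**The concern.** An effect size of 0.50 is the usual medium value for a standardised mean difference. For two independent groups, two-sided 0.05 and 90% power, that value leads to a total well above 100, so 44 looks too small by a factor of about four. A factor of four is what separates a one-group paired calculation from a two-group calculation at the same standardised effect.

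This is the article's only power statement. The Discussion makes a positive result on validity and effect a possible basis for a phase III randomised trial. If the analysable number were near the stated minimum, a null result would carry a claim of 90% power against a medium effect that the design does not have.

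**Working it through.** **Inputs from the protocol article:** effect size 0.50, two-sided alpha 0.05, power 0.90, N at least 44, two groups, ANCOVA on pretest and posttest POS. **Assumptions:** equal numbers of residents per group; pre-post correlation r, varied because the article gives none.

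**1. Reproducing 44.** Paired or one-sample t-test: noncentrality = dz × √n, with n − 1 degrees of freedom.
- n = 43: power 0.8931.
- n = 44: 0.50 × √44 = 3.317, power 0.9000.

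So 44 is exactly the smallest n that reaches 90% with the stated inputs.

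**2. The planned comparison without covariate gain.** Two-sample t-test: noncentrality = d × √(n₁n₂/(n₁ + n₂)).
- 85 per group: power 0.8999.
- 86 per group: power 0.9032, so 172 in total. The ANCOVA F-test at f = 0.25, which is d = 0.50 for two equal groups, gives 171.
- 22 per group: 0.50 × √(484/44) = 0.50 × √11 = 1.658, power 0.367.

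The squared noncentrality at N = 44 is 11.0 for the paired test and 2.75 for the two-group test, which is the factor of four.

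**3. Gain from the pretest.** Adjustment divides the residual variance by 1/(1 − r²), so the effective difference is d/√(1 − r²) and the squared noncentrality becomes 2.75/(1 − r²) at N = 44. At r = 0.5 it is 2.75/0.75 = 3.67; at r = 0.7 it is 2.75/0.51 = 5.39.

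| Assumed r | Power, 44 in total | Power, 44 per group | Total N for 90% |
|---|---|---|---|
| 0 | 0.367 | 0.640 | 171 |
| 0.3 | 0.397 | 0.681 | 155 |
| 0.5 | 0.464 | 0.763 | 129 |
| 0.7 | 0.621 | 0.901 | 88 |
| 0.8 | 0.770 | 0.972 | 63 |

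With equal groups, 171 and 129 round up to 172 and 130.

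**4. What would make 44 in total correct.** The squared noncentrality must reach about 11.
- Through the correlation: 2.75/(1 − r²) = 11 gives r² = 0.75, r = 0.866, where power is 0.899. So r must be about 0.87.
- Through the effect: d² × 11 = 11 gives d = 1.0.

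**5. Other routes to a number near 44.**
- ANCOVA with f = 0.50: power 0.8994 at 44, so the smallest N is 45. But f = 0.50 is d = 1.0, which is not a medium effect.
- Group-by-time interaction with f = 0.25, two measurements and r = 0.5: squared noncentrality 0.0625 × 44 × 2/0.5 = 11, power 0.8997 at 44, so again 45. The effect entered would be 0.25, not the stated 0.50, and it corresponds to a between-group difference in change of 1.0 SD.

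**The case against.** Several points on the other side have force.

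- **No single power figure follows from the text.** A reader might infer that the true power is 37%. That holds only if the pretest explains nothing, or if 0.50 is already expressed in residual SD units. ANCOVA on pretest-posttest data is planned, so a range is the defensible statement. This stands.
- **The paired test is an inference.** A reader might take it as established that the wrong test was chosen in the software. The article names none, and two between-group routes come within one resident of 44. This also stands. Neither route yields exactly 44, however, and neither fits a medium effect of 0.50.
- **Total or per group is open.** Total is the plainer reading. If 44 was per group, 90% is reached at r of about 0.7, but no such correlation is stated.
- **44 is a floor.** A reader might infer that the study will end with about 44 residents and be underpowered. The text says at least 44, and all eligible residents of the homes are assessed; 44 over 30 homes is about 1.5 per home. The documents do not support a forecast of the final number, so the fault lies in the stated figure and not in the enrolment plan.
- **Deaths and clustering.** Allowances for these are detail that a condensed article may leave to the full protocol, and no rate of loss to the posttest is given. Their absence is not counted here as an error.

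The exploratory label does not answer the point, because the article chose to print a specific power claim.

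**Conclusion.** The sample-size statement is wrong as written. Its own inputs do not give 90% power for the planned between-group ANCOVA with 44 residents. At a between-group difference of 0.50 SD the requirement is about 172 in total without covariate gain, roughly two-thirds to three-quarters of that with modest gain, and about half at r = 0.7. At 44 in total, power lies between about 37% and 62% for r from 0 to 0.7; at 44 per group, between 64% and 90%.

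These figures assume equal groups, independent residents and complete POS pairs. The correlations are illustrative, not taken from the article. Deaths before the posttest and similarity of residents within a home could only lower the power for a given number included, but the documents give no figures from which to say by how much.

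The conclusion concerns the claim made for the minimum number. It does not extend to how many residents the study will analyse or to which calculation the authors ran.

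**What to change.** Rewrite the sample-size paragraph for the between-group ANCOVA on POS. Name the test and the effect measure, say whether the number is a total or per group, and state the assumed pre-post correlation. Then choose one of two courses:

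- Give the number of residents with analysable POS data that matches 90% power at 0.50, for example 172 without covariate gain or 130 at r = 0.5, with stated allowances for deaths before the posttest and for clustering by home.
- Keep 44 as a floor with its true power (about 37% to 62% in total for r from 0 to 0.7, or 90% only for a difference of about 1.0 SD without covariate gain), and report the effect detectable with the number expected from the 30 homes after the same allowances.

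The cost is rewording and a less favourable stated figure. Enrolment, data collection and the planned analysis stay as they are, since all eligible residents are already to be included.

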### Outcome measures

#### The effect of the interRAI PC instrument on the quality of palliative care

The multinational consortium interRAI has developed the interRAI PC instrument in order to improve palliative care for elderly
[17]. In order to test this in practice, the effect of the interRAI PC on the quality of palliative care is evaluated.

**Psychometrics** An effect or impact evaluation assesses changes that can be attributed to a particular intervention, such as a project, program or policy, both the intended ones, as well as ideally the unintended ones
[29].

**Data collection** Before the intervention period starts, both experimental and control nursing homes fill out the Palliative care Outcome Scale (POS) for all nursing home residents with palliative care needs. The POS is a ten-item outcome measure that assesses the quality of care in palliative patients
[30]. The instrument contains items on physical, psychosocial and spiritual aspects. There are two versions of the instrument: the POS-Staff version and the POS-Patient version. In this study, we will use the POS-Staff version. The POS can also be used to assess persons with moderate to severe dementia
[31]. The POS is a multidimensional scale that shows good psychometric properties. By means of the POS, the quality of care can be evaluated
[32].

In addition, the experimental and control nursing homes fill out a Retrospective Information (RI) document. This document will provide data on the number of deaths in the past year, the place of death and the availability of a specific palliative care record.

After one year, both experimental and control nursing homes fill out the Palliative care Outcome Scale (POS) and the Retrospective information (RI) document for all nursing home residents with palliative care needs.

**Analysis** Quantitative data are analyzed with SPSS, using independent analysis of covariance (ANCOVA). Research has shown that ANCOVA with pretest-posttest data is the most appropriate statistical procedure in quasi-randomized control-group designs
[33].

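### The ANCOVA for the effect question has no term for nursing home, although whole homes receive the intervention, so its standard errors are too small and the 5% error rate is not held

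*Protocol article*

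**What the plan says.** Under Phase II: Exploratory trial, the unit of allocation is the home. The design is described as "quasi-random assignment to the intervention or control nursing homes". On delivery it says "The fifteen experimental nursing homes receive the intervention that is being tested", and on the comparison group "fifteen care homes which match the intervention nursing homes regarding to facility size, ownership and geographic region are contacted". Table 1 shows that delivery is organisational: staff training, a work group, completion of the instrument by several disciplines, team discussion and care planning.

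The outcome is at resident level. In the section on the effect of the interRAI PC on quality of palliative care, homes of both groups "fill out the Palliative care Outcome Scale (POS) for all nursing home residents with palliative care needs", using the staff version, before the intervention and again after one year. The sample size is also in residents: "this study aims at including at least 44 nursing home residents with palliative care needs". Its basis is given as "Calculations are based on a medium effect size of 0.50, a two-sided significance level of 0.05 and a power of 0.90".

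The Analysis paragraph of the same section names one method: "Quantitative data are analyzed with SPSS, using independent analysis of covariance (ANCOVA". It then defends ANCOVA as the best-suited procedure for quasi-randomised designs with a control group. The article does not mention correlation within homes, an ICC, a design effect or a home-level model. The limitations in the Discussion cover non-random assignment and representativeness, but not clustering.

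**The concern.** An ordinary ANCOVA assumes that the errors of the analysed units are independent. Residents of one home share staff, care culture and the people who score the POS, so a positive correlation within homes is plausible even after adjustment for baseline. If it is present, part of the difference between groups is chance variation between 15 and 15 homes, and the resident-level model counts this variation as if it averaged out over all residents. Its p-values are then too small and its confidence intervals too narrow.

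This is the only test of the study's first aim. The Discussion makes a favourable result on validity and effect the basis for a phase III trial and broader implementation, so a false positive would have a direct consequence.

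**Working it through.** **Unit of analysis.** The protocol does not state it. It follows from POS being scored per resident and from a target of 44, which cannot refer to 30 homes.

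**The plan's own figure.** Inputs from the Sample size paragraph: effect size 0.50, two-sided 0.05, power 0.90.
- Paired or one-sample t-test, standardised difference 0.50: n = 44, power 0.9000. This reproduces the stated figure exactly.
- ANCOVA with two groups, one covariate and Cohen's f = 0.50: N = 45 (power 0.906; N = 44 gives 0.899).
- Two independent groups, d = 0.50: 86 per group, 172 in total. With 22 per group, power is about 0.37.

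The two calculations that reach or nearly reach 44 treat residents as independent, so the figure carries no allowance for clustering.

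**Error rate under clustering.** Let m be the residents analysed per home and ρ the ICC of posttest POS after adjustment for baseline. Both are assumptions. The only m that the protocol implies is its minimum, 44/30 = 1.47.

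Design effect: DE = 1 + (m − 1)ρ. Model standard error as a fraction of the true one: 1/√DE. True two-sided error rate: α = 2[1 − Φ(1.96/√DE)].

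Example, m = 10 and ρ = 0.10: DE = 1 + 9 × 0.10 = 1.90; 1/√1.90 = 0.725; 1.96 × 0.725 = 1.42; α = 0.155.

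| m | ρ = 0.01 | 0.05 | 0.10 | 0.15 | 0.20 |
|---|---|---|---|---|---|
| 1.47 | 0.051 | 0.053 | 0.055 | 0.058 | 0.061 |
| 5 | 0.055 | 0.074 | 0.098 | 0.121 | 0.144 |
| 10 | 0.061 | 0.104 | 0.155 | 0.201 | 0.242 |

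**Check by simulation.** Setting: 15 + 15 homes, no true effect, pre-post correlation 0.5, 3000 runs per cell. The resident-level ANCOVA at m = 10 rejected in 0.059, 0.113, 0.148 and 0.242 of runs for ρ = 0.01, 0.05, 0.10 and 0.20. The formula agrees within Monte Carlo error; for example, √(0.15 × 0.85/3000) = 0.0065. An ANCOVA on home means, over all the settings simulated, rejected in 0.044 to 0.057.

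**Effect of the matching.** At m = 10 and ρ = 0.10, the resident-level rejection rate of 0.148 fell to 0.095 when half of the between-home variance was shared within matched pairs, and to 0.035 when all of it was. Leaving the matching out therefore works against the inflation. The home-means ANCOVA without matching terms became conservative in the same two cases (0.029 and 0.008).

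**The case against.** The strongest objections concern size and reading.

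- *Independent* may mean no more than a between-groups ANCOVA. That is plausible, but it does not help: an ordinary ANCOVA assumes independent errors under either reading.
- The detail might sit in an analysis plan that is not shown. An ICC or a matching specification could. Here, however, the article names the method and argues for it, and a plan that followed this text would carry the fault forward.
- At the one sample size the protocol states, the inflation is small. This stands. Residents are selected because death within 6 to 12 months would not surprise, and the posttest comes at one year, so deaths will reduce the number per home with both scores. On the other hand, the plan is to include all eligible residents of 30 homes, and 44 is a minimum, so several per home is a realistic case.
- Adjustment for baseline POS removes part of the stable differences between homes, so the relevant ICC could be low. This too stands, and it is why the range starts at 0.01.
- This is an exploratory comparison of self-selected homes, as the authors disclose, so correct standard errors would not secure a valid 5% test of the intervention. That is true, but it is a separate weakness and no reason to keep the wrong standard error.

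A reader might also infer that ignoring the matching contributes to the small standard errors. The simulation shows the opposite direction. Nor does the protocol describe formal pairs; it says only that control homes match on three factors.

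**Conclusion.** The concern holds. The named analysis does not fit a design in which whole homes receive the intervention. With any positive correlation within homes and more than one resident per home, it understates the standard error, unless the matching accounts for most of the between-home variance.

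The size cannot be fixed from the document. Under the stated assumptions the true error rate is about 0.051 to 0.061 at 44 residents over 30 homes (ICC 0.01 to 0.20), 0.07 to 0.12 at 5 per home and 0.10 to 0.20 at 10 per home (both ICC 0.05 to 0.15). These figures ignore the matching and are upper values to the extent that size, ownership and region explain differences between homes.

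A reader might go further and conclude that the study in effect has about 30 observations. The figures do not support this in general. At 5 per home, 150 residents divided by design effects of 1.2 to 1.6 leave 125 to 94. At 10 per home and ICC 0.05, 300/1.45 = 207. Only at the higher ICCs with larger homes does the effective number come closer to 30 than to the number of residents.

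**What to change.** In the Analysis paragraph, replace the ANCOVA with a linear mixed model of posttest POS on group, baseline POS and the matching factors (facility size, ownership, region), with a random intercept for home and Satterthwaite or Kenward-Roger degrees of freedom. An ANCOVA on home-level means, with the matching factors included, is an acceptable alternative. The two are not equivalent, so one should be named as primary. Deleting the word *independent* alone would change nothing.

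Restate power for this clustered two-group comparison with an assumed ICC and number of residents per home. Do not multiply 44 by a design effect, because 44 fits a paired or one-sample test. For orientation, the unadjusted two-group total of 172 at 10 per home becomes 172 × 1.45 ≈ 250 residents at ICC 0.05 and 172 × 1.90 ≈ 327 at ICC 0.10.

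The cost is a change of wording, a home identifier for each resident and wider confidence intervals. SPSS fits mixed models, and no further outcome data are needed. The change does not remove selection bias from homes that volunteered.

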#### Feasibility of the interRAI PC instrument

Research has shown that an intervention, in order to be worthy of testing for efficacy, should answer the relevant questions within feasibility: ‘Can it work?’, ‘Does it work?’, ‘Will it work?’
[34].

**Psychometrics** Feasibility is defined as the convenience and suitability to use an instrument
[35].

**Data collection** Focus groups and interviews with the multidisciplinary nursing home staff of participating nursing homes are organized. Caregivers are asked to answer questions concerning the length of the instrument, barriers, facilitators, completion time, planning, etc.

**Analysis** Qualitative data analysis will be conducted using the NVivo software©.

#### Face validity of the interRAI PC instrument

Based on a systematic review, we found that the interRAI PC instrument is the most comprehensive geriatric assessment for nursing home residents with palliative care needs
[19]. In order to take this finding further into practice, the face validity of the interRAI PC will be evaluated.

**Psychometrics** Face validity refers to the degree to which an instrument appears to reflect the variable it has been designed to measure
[36].

**Data collection** Focus groups and interviews with multidisciplinary nursing home staff of participating nursing homes are organized to evaluate the face validity of the instrument. Caregivers are asked whether items, CAPs and scales are lacking, redundant and clear enough.

**Analysis** Qualitative data analysis will be conducted using the NVivo software©.

